**16. Data Collection Tools**

- Recording sensory evoked potentials with the EMG/NCV/EP5000 Q device
- Recording motor evoked potentials with the TMS MagPro X100 device
- Assessment of low back motor control using Luomajoki clinical tests
- Measurement of disability using the Persian version of the Oswestry Disability Index questionnaire
- Measurement of pain with the Visual Analog Scale (VAS)
- Cognitive assessment using the Mini Mental Status Exam (MMSE)
- Recording demographic and clinical characteristics with a designed questionnaire
- Consent form

**17. Procedure**Initially, the study will receive an ethics code and will be registered in the IRCT system to obtain a clinical trial code. Participants who meet the study criteria will be given detailed explanations about the research procedures so they have a full understanding of how the study will be conducted. Each participant will provide informed consent by signing a written consent form approved by the Tehran University of Medical Sciences Ethics Committee. Assessments will be conducted first, followed by treatments in the control group (sensory-motor exercises combined with sham transcranial electrical stimulation) and the intervention group (sensory-motor exercises combined with real transcranial electrical stimulation) for 4 weeks. Reassessment will occur 24 to 48 hours after the last treatment session.

**17-1. Assessment**
Assessments will be performed before the first treatment session and 24 to 48 hours after the completion of the treatment. Two laboratory tests and one clinical test will be conducted, and two questionnaires will be completed.

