**13. Sample Size**

The sample size was calculated using G*Power 3.1.3 software, based on the Jafarzadeh et al. study [28], with pain as the primary outcome measure. The calculation used a between-group Cohen's f of 0.473, a power of 0.8, and an α of 0.05. This power analysis indicated that at least 30 participants were needed. To account for a potential 15% dropout rate, 34 participants were recruited.

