Bipolar electrodes for stimulation will be placed on the lower back, 3 centimeters lateral to the spinous process of L3, on the same side as the most pain. Electrical stimuli will have a pulse duration of 1 millisecond and will be applied at a frequency of 2 Hz. The bandwidth will be set from 1 to 500 Hz. Stimulation intensity will start at 1 milliampere and increase by 1 milliampere until the perceptual threshold is reached. Then, the stimulation intensity will be set to three times the perceptual threshold. If this intensity causes pain, the stimulation intensity will be decreased by 1 milliampere until it is no longer painful. Stimuli will be applied 500 times, and this process will be repeated twice, with the average of the two repetitions used in the final analysis. The maximum amplitude of sensory evoked potentials will be below 10 microvolts. The amplitude N80 is the largest peak in the 40 to 90 milliseconds range from the onset of the wave, while the amplitude N150 is the largest peak in the 90 to 180 milliseconds range, though in this study, N80 and N150 were observed more in the 65 and 120 milliseconds ranges. As shown in the figure, the maximum amplitude is the difference between the highest peak and the lowest trough.

[figure not shown]
Top of Form

Bottom of Form

Fig 1. Sensory-evoked potentials (N80 and N150)

[figure not shown]

Fig 2. N80 and N150 Amplitudes

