**17-1-1-2. Test for Brain Motor Processing**

To assess brain motor processing, motor threshold and motor evoked potentials will be measured using the TMS MagPro X100 device. Generally, the goal of motor evoked potentials is to evaluate the motor nervous system by applying a single stimulating pulse through transcranial magnetic stimulation to the motor cortex and then recording this motor stimulation from the corresponding muscle using electromyography electrodes. The recorded wave is known as the motor evoked potential.

Motor threshold will also be an index of cortical excitability and will be used to determine the intensity of stimulation with the device.

In this test, four variables (active motor threshold and amplitude of motor evoked potentials for the multifidus muscle and abdominal transverse) will be examined. These variables are indicators of excitability, performance, and the integrity of neural pathways and corticospinal areas related to these muscles.

For recording variables related to the multifidus muscle, the patient will sit comfortably on a chair with their feet on the ground. A surface electromyography electrode will be placed on the spinous process of L5, aligned with a line connecting the PSIS and the L1-L2 space. The ground electrode will be placed on the iliac crest. The bandwidth will be set from 5 to 500 Hz. To achieve maximal contraction in the multifidus muscle, the participant will be asked to perform a trunk extension against resistance and hold it for 3 seconds. This movement will be repeated 3 times, and the maximum contraction will be measured based on the Root Mean Square (RMS) within a 1-second window. Then, 20% of this value will be used as the submaximal contraction, which will be displayed on a monitor for the participant to maintain throughout the recording. This contraction is intended to facilitate the recording of motor evoked potentials in the paravertebral muscles. In other words, if the muscle is in a resting state, recording will be difficult.

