**17-1-2-3. Pain Level**

To evaluate pain intensity, the Visual Analog Scale (VAS) will be used. This scale consists of a 10 cm line, where the individual rates their pain from 1 to 10. Zero represents no pain, and ten represents unbearable pain (48). This scale is a discrete quantitative measure used to assess changes in pain intensity before and after interventions.

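### A cheap gain in precision: rate pain, the outcome that sizes the trial, before the tests at each visit and average three ratings

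*Protocol*

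**What the plan says.** Protocol section 13 bases the sample size on a calculation "with pain as the primary outcome measure". It adds: "The calculation used a between-group Cohen's f of 0.473, a power of 0.8, and an α of 0.05", and "This power analysis indicated that at least 30 participants were needed".

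Section 17-1 sets two assessments, one before treatment and one 24 to 48 hours after it ends, and lists their content: "Two laboratory tests and one clinical test will be conducted, and two questionnaires will be completed". The subsections keep that grouping: laboratory tests in 17-1-1, then movement control, disability and, last, pain in 17-1-2.

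Section 17-1-2-3 on pain says: "This scale consists of a 10 cm line, where the individual rates their pain from 1 to 10". It gives no number of ratings, no averaging, no recall period and no timing relative to the other tests.

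The laboratory tests act on the lower back:
- **Sensory test (17-1-1-1).** Electrodes sit beside L3 on the more painful side. "Stimuli will be applied 500 times, and this process will be repeated twice", and the two runs are averaged. If the chosen intensity hurts, it is stepped down until it does not.
- **Motor test (17-1-1-2).** For the multifidus, "the participant will be asked to perform a trunk extension against resistance and hold it for 3 seconds". This is done three times. A contraction at 20% of maximum is then held during recording, which includes a threshold search that starts at 25% of device output and rises by 2% per step.

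**The concern.** Pain carries the sample size, yet its measurement is described more thinly than that of the secondary outcomes. The evoked potentials are averaged over two runs, and eligibility (section 14) uses average pain intensity. The outcome rating has no averaging rule.

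Two sources of avoidable noise follow. A single rating carries all of a patient's short-term fluctuation. And if a site followed the listed order, patients with disc herniation and radicular pain would rate their pain after resisted extensions, a held contraction and repeated stimulation of the painful side. Some might be stirred up by this at one visit and not the other. Either source widens the error term of the pain comparison in a trial planned on 30 evaluable patients.

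**Working it through.** **Inputs from the protocol.** f = 0.473, α = 0.05, target power 0.8 and N = 30 (section 13); two groups in balanced blocks, taken as 15 per arm (17-2); two visits (17-1); a group by pre/post mixed ANOVA (18). For two equal groups d = 2f = 0.946.

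**Inputs assumed, because the protocol gives none.** Pre-post correlation ρ = 0.5; reliability of one rating R = 0.7, 0.8 or 0.9; independent errors between ratings; SD of test-provoked pain s = 0.1, 0.25 or 0.5 of the pain SD, independent between visits.

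**Step 1: reproduce N = 30.** Section 13 does not name the test. The between-group F test for two repeated measurements has noncentrality λ = N f² × 2/(1 + ρ) = 30 × 0.2237 × 2/1.5 = 8.95. On 1 and 28 degrees of freedom the power is 0.823. With N = 28 it is 0.794, so 30 is the smallest even total that reaches 0.8. A two-sided comparison at one visit would need 38. The stated 30 therefore fits the repeated-measures between-group test at ρ = 0.5.

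**Step 2: the group-by-time test.** With equal baselines and a post-treatment difference d, λ = (N/4) d² / [2(1 − ρ)] = 7.5 × 0.8949 / 1 = 6.71, and power is 0.706.

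**Step 3: mean of three ratings per visit.** The variance relative to one rating becomes v = R + (1 − R)/3, and the pre-post covariance stays at 0.5. Then λ(main) = 13.42/(v + 0.5) and λ(group-by-time) = 6.71/[2(v − 0.5)].

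| R | v | λ main | Power main | λ group-by-time | Power group-by-time |
|---|---|---|---|---|---|
| one rating | 1.000 | 8.95 | 0.823 | 6.71 | 0.706 |
| 0.7 | 0.800 | 10.33 | 0.873 | 11.19 | 0.898 |
| 0.8 | 0.867 | 9.82 | 0.857 | 9.15 | 0.832 |
| 0.9 | 0.933 | 9.37 | 0.840 | 7.74 | 0.766 |

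**Step 4: what test-provoked pain could cost, if it occurs.** A constant shift drops out of the group comparison. Variation by patient and visit gives v = 1 + s² in the same formulas.

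| s | v | Power main | Power group-by-time |
|---|---|---|---|
| 0.1 | 1.010 | 0.821 | 0.697 |
| 0.25 | 1.0625 | 0.808 | 0.655 |
| 0.5 | 1.250 | 0.762 | 0.533 |

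Up to a quarter of the pain SD, the loss is under 2 points for the main effect and about 5 for group-by-time. At half the pain SD it is about 6 and 17 points.

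**The case against.** The strongest reply is that nothing here is stated wrongly. Section 17-1 reads as an inventory. Where the protocol means a sequence it says so, as in section 17 (assessment before treatment) and sections 17-2-1 and 17-2-2 (stimulation before exercise). Section 12 names two locations, so even one continuous battery is an assumption. This stands: a reader might infer that pain is rated after the tests, but the text does not say so.

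A reader might also infer that the tests provoke pain and so reduce power. The protocol does not show this. The electrical stimulus is lowered if it hurts, and both arms undergo the same tests at both visits. No such safeguard is stated for the resisted extensions or the held contraction, so the risk remains open, but its size is unknown.

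A third tempting reading is that 0.706 against the planned 0.80 is a loss caused by the pain measurement. It is not. The gap between 0.823 and 0.706 comes from which effect is tested, at the same single-rating variance. Moreover, if the effect size from the cited study was itself based on single ratings, their noise is already in the planned power.

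Two further points stand. The rating is a single one only in that the protocol mentions no other, and it is nowhere called momentary. And the gain in step 3 shrinks if ratings close in time share their errors.

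**Conclusion.** The point holds as a cheap improvement to how the sizing outcome is measured, not as an error in the calculation or a demonstrated loss of power. The protocol describes one VAS per visit, without averaging or recall period, and leaves open whether it precedes or follows tests that load the painful back.

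Under the assumptions above, averaging three ratings adds about 6 to 19 points of power for group-by-time and about 2 to 5 points for the group main effect, with the same 30 patients. These are gains over the plan and upper figures if rating errors are correlated. Rating before the tests removes a possible loss that cannot be sized from the protocol.

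**What to change.** In section 17-1, state that at both visits the VAS and the Oswestry questionnaire are completed on arrival, before any stimulation, contraction or movement test.

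In section 17-1-2-3, define the pain outcome as the mean of three VAS ratings with one fixed recall period, collected in the same way at both visits and all before the tests. After treatment, all three must fall within the existing 24 to 48 hour window. Ratings taken over the whole day before the visit would not do: for a patient seen at 24 hours they would reach back to the last treatment session. A rule for a missing rating should be given, for example the mean of those available.

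The cost is a few minutes of patient time, some risk of a missing rating, and a tighter choice of visit time if the ratings are spread within the window. Taking them close together avoids that constraint but gives up part of the gain. No extra patients or assessment visits are needed.

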**17-1-1. Laboratory Assessments**
The laboratory assessments will include two tests: one to evaluate brain sensory processing and the other to evaluate brain motor processing.

**17-1-1-1. Test for Brain Sensory Processing**
To assess brain sensory processing, sensory evoked potentials will be recorded using the EMG/NCV/EP5000 Q device. Generally, sensory evoked potentials evaluate the sensory nervous system by applying somatosensory stimuli to record brain waves using electroencephalography electrodes. Electroencephalography reflects the brain's spontaneous electrical activity over a short period, whereas sensory evoked potentials are not recorded spontaneously but are associated with pre-stimulation.

In this test, two variables (amplitude N80 and N150) will be analyzed. Electrophysiological research shows that sensory evoked potentials recorded by electroencephalography reflect the processing of afferent sensory pathways in distinct areas of the brain cortex. The N80 time window is believed to represent processing in the primary sensory cortex (S1), while the N150 time window reflects processing in the secondary sensory cortex (S2).

For the test, participants will sit comfortably on a chair with their feet on the ground and hands relaxed. Participants will be asked to sit with their eyes closed but remain awake during the test. Sensory evoked potentials will be recorded using surface electrodes placed on the scalp. These electrodes will be positioned on the S1 area, 3 centimeters lateral to Cz and 2 centimeters posterior, and on the opposite side of the participant’s pain location. The scalp at the recording site should not have more than 5 kilo-ohms resistance. The reference electrode will be placed at Fz and the ground electrode on the forehead.

Bipolar electrodes for stimulation will be placed on the lower back, 3 centimeters lateral to the spinous process of L3, on the same side as the most pain. Electrical stimuli will have a pulse duration of 1 millisecond and will be applied at a frequency of 2 Hz. The bandwidth will be set from 1 to 500 Hz. Stimulation intensity will start at 1 milliampere and increase by 1 milliampere until the perceptual threshold is reached. Then, the stimulation intensity will be set to three times the perceptual threshold. If this intensity causes pain, the stimulation intensity will be decreased by 1 milliampere until it is no longer painful. Stimuli will be applied 500 times, and this process will be repeated twice, with the average of the two repetitions used in the final analysis. The maximum amplitude of sensory evoked potentials will be below 10 microvolts. The amplitude N80 is the largest peak in the 40 to 90 milliseconds range from the onset of the wave, while the amplitude N150 is the largest peak in the 90 to 180 milliseconds range, though in this study, N80 and N150 were observed more in the 65 and 120 milliseconds ranges. As shown in the figure, the maximum amplitude is the difference between the highest peak and the lowest trough.

[figure not shown]
Top of Form

Bottom of Form

Fig 1. Sensory-evoked potentials (N80 and N150)

[figure not shown]

Fig 2. N80 and N150 Amplitudes

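### A sensory stimulus rate of exactly 2 Hz divides the mains frequency evenly, so averaging removes mains interference from N80 and N150 less well than it could; a slightly different rate would cost almost nothing.

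*Protocol*

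**What the plan says.** Protocol 17-1-1-1 fixes the recording of N80 and N150 as follows.

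- Stimulus: "Electrical stimuli will have a pulse duration of 1 millisecond and will be applied at a frequency of 2 Hz". No jitter of the interval is mentioned.
- Filter: "The bandwidth will be set from 1 to 500 Hz". No notch filter or other mains rejection is mentioned.
- Averaging: "Stimuli will be applied 500 times, and this process will be repeated twice, with the average of the two repetitions used in the final analysis".
- Signal size: "The maximum amplitude of sensory evoked potentials will be below 10 microvolts".
- Reading: "The amplitude N80 is the largest peak in the 40 to 90 milliseconds range from the onset of the wave", with 90 to 180 ms for N150, and "the maximum amplitude is the difference between the highest peak and the lowest trough".
- Electrode contact: "The scalp at the recording site should not have more than 5 kilo-ohms resistance". The reference is at Fz and the ground on the forehead.

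N80 and N150 amplitudes are secondary outcomes (sections 3 and 4). Section 18 compares them by a mixed ANOVA of group and time, and uses the neurophysiological parameters in correlations with the clinical ones.

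**The concern.** Averaging over sweeps removes only activity that is out of step with the stimulus. If the interval between stimuli holds a whole number of mains cycles, each sweep starts at about the same mains phase, and the interference adds up along with the response.

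The reading rule makes this matter more. A peak-to-trough difference picks up the high and the low point of any sine wave left in the window, so a residual tends to enlarge the amplitude. Its phase, and its size through electrode contact, can differ from visit to visit, so it also adds noise to the pre-post change.

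N80 and N150 are the trial's only measures of sensory cortical processing. With 34 participants recruited (section 13), avoidable measurement noise weakens both the secondary group comparisons and the correlations.

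**Working it through.** **Inputs from Protocol 17-1-1-1.** Rate r = 2 Hz, N = 500 sweeps per run, two runs, band 1-500 Hz, windows 40-90 ms and 90-180 ms.

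**Assumptions, because the protocol is silent.** Mains is 50 Hz, with 60 Hz shown as the alternative. The stability of the mains frequency, the raw mains level at the scalp and the presence of a notch filter are unknown.

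**Step 1: cycles per interval (f/r).**
- 2.0 Hz: 50/2 = 25 and 60/2 = 30. Both are whole numbers, so the result does not depend on which mains frequency is assumed.
- 2.1 Hz: 50/2.1 = 23.81 and 60/2.1 = 28.57.
- 1.9 Hz: 50/1.9 = 26.32 and 60/1.9 = 31.58.

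**Step 2: share of mains left after one run at nominal frequency.** The share is |(1/N) Σ exp(2πi·f·k/r)|, k = 0 to 499.

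| Rate | 50 Hz mains | 60 Hz mains |
|---|---|---|
| 2.0 Hz | 100% | 100% |
| 2.1 Hz | 0.24% | 0.16% |
| 1.9 Hz | 0.08% | 0.21% |

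For comparison, noise with a random phase in each sweep leaves 1/√500 = 4.5%.

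**Step 3: steady offset d from nominal, at 2 Hz.** A run lasts 500/2 = 250 s, and the share left is close to |sin(250πd)|/(250πd).

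| d (Hz) | Share left |
|---|---|
| 0.001 | 90% |
| 0.002 | 64% |
| 0.004 | 0% |
| 0.01 | 13% |
| 0.03 | 4.2% |
| 0.05 | 2.5% |

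The envelope is 1/(250πd). It falls below the random-phase 4.5% at about 0.03 Hz and stays below it from there on.

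**Step 4: slowly wandering mains at 2 Hz.** The frequency was simulated as a slow random process around 50 Hz with a 60 s time constant. The mean share left after one run was 51%, 36%, 24-25% and 15% for SD 0.005, 0.01, 0.02 and 0.05 Hz. Time constants of 30 to 300 s gave medians of 39-57%, 28-35%, 18-24% and 11-15% for the same SDs. At 1.9 or 2.1 Hz the medians stayed at or below 0.26%.

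**Step 5: the second run.** The protocol does not say whether the two waveforms or the two amplitudes are averaged. If waveforms are averaged, the 15-51% of step 4 falls to about 11-36% (60 s gap between runs assumed). If only amplitudes are averaged, the mean inflation stays and its noise falls.

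**Step 6: effect on the reading.** A 50 Hz cycle lasts 20 ms. The windows hold 50/20 = 2.5 and 90/20 = 4.5 cycles, so both contain a peak and a trough of any residual. The size in microvolts needs assumed values. With 1-5 µV of raw mains, the one-run residual at 2 Hz is between 0.15 × 1 = 0.15 µV and 0.51 × 5 = 2.55 µV. At 1.9 or 2.1 Hz it is at most about 0.0025 × 5 = 0.013 µV. On illustrative waves of 2.3 µV with random mains phase:

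- a 0.15 µV residual raised the N80 reading by 0.05 µV on average, with an SD of 0.15 µV across phases;
- a 0.5 µV residual raised N80 by 0.5 µV and N150 by 0.85 µV on average.

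On larger illustrative waves of 3-5 µV, a 0.15 µV residual added only 0.01-0.09 µV.

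**The case against.** The strongest reply is that nothing in the protocol shows mains to be a problem here. The harm depends on three unknowns: the raw mains level, how steady the mains frequency is, and whether the device applies a notch filter. A stated 1-500 Hz band does not exclude a separate notch. If raw mains is a fraction of a microvolt, the effect is negligible at any rate. The 5 kilo-ohm limit also restrains the variation in electrode contact through which interference would differ between visits. This stands, and it is why no microvolt figure can be claimed for this trial.

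It is also fair that real mains is not locked to the stimulator. Wander of the assumed size already removes about half or more of the interference, a steady offset of 0.03 Hz or more does as well as random phase, and a small error in the stimulator clock acts in the same way as an offset. This limits the claim but does not remove it. Under wander the mean residual at 2 Hz stays above 4.5% in every case simulated, and far above that at 1.9 or 2.1 Hz.

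A reader might infer that the N80 and N150 results would be biased in favour of one arm, or that the change scores are biased upwards. The document does not support this. Both arms and both visits use the same settings, so average inflation largely cancels in the group-by-time contrast and mainly extra variance is left. A bias in the change would need contact to worsen or improve systematically between visits, and nothing indicates that.

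**Conclusion.** This is a cheap improvement to a secondary measure, not a demonstrated error. The arithmetic is firm: 2 Hz divides both 50 and 60 Hz evenly. The mains share left after one run is 100% at nominal frequency and about 15-50% under the assumed slow wander (about 11-36% if the two run waveforms are averaged). At 1.9 or 2.1 Hz it is about 0.25% or less. With a steady offset of 0.03 Hz or more, about 4% or less would be left even at 2 Hz.

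The size in microvolts rests on assumptions and may be small. The likely harm is avoidable noise and some inflation of N80 and N150, which weakens the secondary comparisons and the correlations. The primary outcomes (lumbar movement control, disability and pain) are not affected.

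**What to change.** In 17-1-1-1, state a stimulus rate that does not divide the mains frequency (for example 1.9 or 2.1 Hz), or a jittered interval. Leave the number of stimuli and the filters unchanged, and state whether the device's mains filter is on. Use the same setting at both visits of every patient.

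Cost: one device setting. A run of 500 stimuli takes 500/1.9 = 263 s or 500/2.1 = 238 s instead of 250 s.

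There is one downside. The section reports in the past tense where the two peaks were seen in this study, so some recordings may already exist. Any patient recorded at 2 Hz before treatment should be recorded at 2 Hz afterwards too. The rate may then differ between patients, so record it for each patient and check that it is balanced by arm.
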